### Recruitment {15}

Participant recruitment began in June 2021 and is expected to continue until 2023. We will recruit participants in 6 hospitals: Sir Run Run Shaw Hospital Affiliated to Zhejiang University, Hangzhou, Zhejiang, China, in conjunction with investigators at Ningbo Ninth Hospital, Ningbo, China, Zhejiang Xinhua Hospital, Zhejiang, China, Lin’an People’s Hospital, Zhejiang, China, and YuHang Fifth People’s Hospital, Zhejiang, China. Participants will be recruited through poster advertisements and referrals from physicians. Once recruited, researchers will teach the participants how to use the MiniApp.

### Assignment of interventions: allocation

#### Sequence generation {16a}

In this randomized controlled trial, participants will be randomized into either intervention or control arm with an allocation ratio of 1:1. The allocation will be generalized by the establishment of EDC Trial Data clinical trials centralized randomization system. Researchers will enter the system with account numbers and passwords. A randomized number generated by inputting patient information will be used to track each patient.

#### Concealment mechanism {16b}

Allocation concealment will be guaranteed through the following mechanism. Staff will log in to the EDC Trial Data cloud and enter the information for the participants. The EDC Trial Data system will randomly assign participants to either group in a 1:1 ratio. A patient profile will be generated after the necessary baseline information has been entered. Account number and password are required when assessing data.

### Assignment of interventions: blinding

#### Who will be blinded {17a}

Participants and investigators will be aware of the intervention that has been assigned to them in this open-label trial. Because of the nature of the patient-reported outcome measures, not all outcome evaluations will be blinded. During the analysis, the statistician will be blinded to the allocation.

#### Procedure for unblinding if needed {17b}

The procedure for unblinding is not applicable as this is an open-label trial.

### Data collection and management

#### Plans for assessment and collection of outcomes {18a}

Data will be collected utilizing EDC in each site. Data collection takes place at four points: baseline, 1, 3, and 6 months. Collected data will be stored in the form of an electronic case report form. The clinical research coordinator (CRC) will complete the electronic case report form. The investigators will be informed of any changes made by CRC and system/edit check automatically done by the system. Authorized investigators will be permitted to access the study computers and evaluate the data throughout the study.

#### Plans to promote participant retention and complete follow-up {18b}

If any missing data is detected via the EDC system, the researcher will contact the participants by telephone.

#### Data management {19}

Study teams have a responsibility to self-monitor study processes and data. This self-monitoring can ensure a well-run trial and to identify and mitigate issues before they are identified by monitoring entities; which can result in time-consuming fixes. Internal monitoring includes monitoring for proper informed consent documentation/records, eligibility criteria, data quality, etc. Monitoring is usually conducted by interested parties involved in the research to identify issues and to improve processes. A unique identification code will be generated when analyzing data to ensure security. Errors or missing data information will be sent to data managers (DM) in Data Query Reports. DM receiving the inquiry will check the original records to determine the correction. Original paperwork and signed informed consent forms will be stored in locked file cabinets.

#### Confidentiality {27}

Personal information will be collected, shared, and maintained following ICH GCP. Before the start of the research, the principal investigator authorizes the investigators and study nurses the rights to the data set. All participants need to sign the informed consent form for the data to be collected. A randomized number is generated to track each patient. All data will be stored on a secure database (EDC). Only authorized researchers have access to the data set. Authorized researchers only have access to the data collected by themselves. Review of data collected by other researchers is not permitted.

This trial data will not be shared to enable international prospective meta-analyses.

#### Plans for collection, laboratory evaluation, and storage of biological specimens for genetic or molecular analysis in this trial/future use {33}

No genetic or molecular analysis will be conducted in this trial or for future use.

### Statistical methods

#### Statistical methods for primary and secondary outcomes {20a}

Categorical variables will be expressed in numerical values with their respective percentages and compared using the chi-squared test at baseline. Continuous variables will be expressed as mean ± SD and compared using the *t*-test. The significance of primary and secondary endpoints will be evaluated with the paired-samples *t*-test. A *p*-value < 0.05 indicates statistical significance. All data will be analyzed with the SPSS.

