#### Outcomes {12}

Outcomes will be collected at baseline and again at 1, 3, and 6 months during the intervention period.

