### Primary outcome measure

*LDL-C level*. The primary endpoint will be the mean change in LDL-C level [time Frame: from randomization (day 0) to V5 (week 24) for a total of 6 months of treatment]. Per guideline, the LDL-C level has been validated as a primary measurement for the clinical efficacy of the treatments [3].

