### Secondary outcome measures

The percentage of the participants with an LDL < 70 mg/dLThe percentage of the participants with an LDL < 70 mg/dL and an HDL > 500 mg/dLThe ratio of measured LDL to baseline LDLCoefficient of variation of LDLC-reactive protein levelMean change in body mass index (BMI)Mean score of General Self-Efficacy Scale (GSEs). The GSEs is a psychometric scale that assesses optimism in one’s ability to cope with a variety of life’s challenges. It consists of 10 items representing attitudes towards obstacles rated on a scale from 0 (not optimal) to 4 (very optimal). A Chinese version has been validated [19].Mean score of Quality of life index (QL-index). The QL-index is a tool to evaluate quality of life [20]. It was initially established to measure lifestyle factors in cancer patients and is now commonly used in various disease states. Measurements cover: activities of daily living, principal activities, health, outlook, and support [21]. We consider QL-index as valid measurements to evaluate the quality of life in ASCVD patients.

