### Sample size {14}

Considering the primary outcome variable as the reduction in the mean LDL-C from baseline to week 24, an absolute reduction of 20% in LDL-C is expected [22, 23]. One hundred twenty-two subjects per group was calculated initially to offer 80% power at a one-sided 0.05 significance level according to a 1:1 ratio of random grouping. Allowing for a maximum follow-up loss rate of 20% in both groups, 300 patients were determined as the target sample size—150 patients in each group.

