#### Methods for additional analysis (e.g., subgroup analysis) {20b}

No additional analysis will be conducted.

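### The primary change in LDL-C is assigned to t-tests that do not adjust for baseline LDL-C; a between-arm ANCOVA would be more precise and would handle chance baseline imbalance correctly

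*Protocol article*

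**What the plan says.** All references are to the protocol article.

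- **Endpoint** (Primary outcome measure): "The primary endpoint will be the mean change in LDL-C level", from day 0 to week 24.
- **Data** (Outcomes {12}): "Outcomes will be collected at baseline and again at 1, 3, and 6 months during the intervention period". A baseline LDL-C is therefore part of the planned data for every patient.
- **Tests** (Statistical methods {20a}): the general sentence on continuous variables is "Continuous variables will be expressed as mean ± SD and compared using the *t*-test". It follows the sentence on baseline comparisons and does not name the primary endpoint. The sentence that does is "The significance of primary and secondary endpoints will be evaluated with the paired-samples *t*-test".
- **Threshold** ({20a}): "A *p*-value < 0.05 indicates statistical significance", with no mention of one or two sides.
- **Other analyses** ({20b}): "No additional analysis will be conducted".
- **Sample size** ({14}): "One hundred twenty-two subjects per group was calculated initially to offer 80% power at a one-sided 0.05 significance level". No SD and no correlation between visits is given.

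No covariate, ANCOVA or mixed model appears anywhere in these sections.

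**The concern.** A t-test, paired or independent, takes no covariate. The paired test has a more basic problem: read as a comparison of visits within an arm, it does not compare the arms at all, although the trial is designed as a parallel-group superiority trial. Correcting that alone would not settle the present point. The obvious repair is to apply the independent-samples t-test, already named in the sentence before, to the change in LDL-C. Subtracting baseline is not the same as adjusting for it.

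Two things are at stake. First, the interval for the CBT-minus-control difference would be wider than the collected data require. Second, within the trial actually run, an arm that happens to start with higher LDL-C would tend to show the larger fall through regression to the mean, and the change score would credit that to treatment.

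This is not a detail left open for a separate analysis plan. The article itself names the test for the endpoints, and it plans no further analysis in which an adjusted estimate could appear.

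**Working it through.** **Inputs from the article.** 122 per arm, 80% power, one-sided 0.05, 1:1 allocation; 150 per arm recruited with 20% loss allowed. **Assumptions.** The correlation ρ between baseline and week-24 LDL-C is not stated, so a range is shown. SDs at the two visits are taken as equal (σ).

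**1. The plan's own figure.** The 122 cannot be reproduced, because no SD is stated. Working backwards under the normal approximation, 122 per arm implies a standardised difference of

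d = (1.645 + 0.842) × √(2/122) = 0.318.

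If the expected 20% reduction is the between-arm difference, the implied SD is 20/0.318, about 62.8 percentage points. In what follows, d is taken as scaled to the SD of the change, that is, the 80% is read as the power of an independent-samples t-test on change. The article does not say so.

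**2. Variance ratio.** Per-patient variance is 2σ²(1 − ρ) for the change score and σ²(1 − ρ²) for ANCOVA. The ratio is

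(1 − ρ²) / [2(1 − ρ)] = (1 + ρ)/2,

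which is below 1 whenever ρ is below 1.

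**3. Power at 122 per arm, one-sided 0.05.** Power = Φ(2.487/√((1 + ρ)/2) − 1.645). At ρ = 0.5: 2.487/0.866 = 2.871; 2.871 − 1.645 = 1.226; Φ = 0.890. The per-arm number for equal power is 122 × (1 + ρ)/2, rounded up.

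| ρ | Variance ratio | Change score | ANCOVA | Gain (points) | n per arm for 80% with ANCOVA |
|---|---|---|---|---|---|
| 0.3 | 0.65 | 80.0% | 92.5% | 12.5 | 80 |
| 0.5 | 0.75 | 80.0% | 89.0% | 9.0 | 92 |
| 0.7 | 0.85 | 80.0% | 85.4% | 5.4 | 104 |
| 0.8 | 0.90 | 80.0% | 83.5% | 3.5 | 110 |
| 0.9 | 0.95 | 80.0% | 81.8% | 1.8 | 116 |

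A simulation of 20,000 trials at ρ = 0.5 gave 79.6% and 88.9%, in agreement.

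**4. Two variations.** With 20% loss, 150 × 0.8 = 120 per arm remain, and at ρ = 0.5 power is 79.4% (change score) against 88.5% (ANCOVA). If the threshold in {20a} is applied two-sided to a trial sized one-sided, the same d gives 70% for the change score and 82% for ANCOVA at ρ = 0.5, or 77% at ρ = 0.7.

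**5. Chance imbalance.** Let D be the baseline difference, CBT minus control. Given D, the expected difference in change is the treatment effect minus (1 − ρ)D. At ρ = 0.5 the expected slope on D is −0.5 (simulated −0.49); for ANCOVA it is 0 (simulated 0.01). For scale: one standard error of D is σ√(2/122) = 0.128σ, which at ρ = 0.5 moves the change-score estimate by 0.5 × 0.128σ = 0.064σ. At that ρ the change SD equals σ, so the assumed effect is 0.318σ and the shift is 0.064/0.318, about 20% of it.

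**The case against.** The strongest reply is that the power figures describe a test that the article does not assign to the endpoints. The paired test is the named one; the comparison above starts only after it has been replaced, and whoever replaces it can add the covariate at the same time. This stands as far as the figures go: they measure what the natural repair would still lose, not the performance of the plan as written. It does not remove the point, because neither named test adjusts for baseline and the repair most likely to be made would not either.

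It is also fair to say that this concerns efficiency, not validity. Under randomisation, a between-arm comparison of change is unbiased on average and keeps its type I error. And because the Trial status section reports recruitment as completed in January 2022 (Recruitment {15} differs), the smaller sample size under ANCOVA may have little practical use. Both remarks stand; the gain in precision on the data collected is unaffected.

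Three stronger readings are tempting and should not be drawn:

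- **That chance imbalance is left uncorrected.** This would fit a t-test on week-24 values. The endpoint is a change, which over-corrects by (1 − ρ) times the imbalance.
- **That baseline goes unused for the secondary scores.** A reader might infer this from "Mean score of General Self-Efficacy Scale (GSEs" and the similar wording for QL-index. But {20a} assigns the paired test to secondary endpoints too, and if the pairing is baseline with follow-up, baseline is used. What is missing is adjustment in a between-arm comparison.
- **That nine points of power are lost.** That is the value at ρ = 0.5 only.

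**Conclusion.** The point holds as a worthwhile improvement. Baseline LDL-C is collected, the endpoint is a change from it, and the analysis named in the article adjusts for it nowhere. Relative to an independent-samples t-test on change, ANCOVA has the smaller variance at every ρ below 1, by the factor (1 + ρ)/2. Over ρ from 0.3 to 0.8 this is worth 12.5 down to 3.5 points of power.

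The variance ratio and the over-correction follow from theory and are firm under equal SDs. The power figures are conditional: ρ is assumed, the 80% starting point cannot be checked without an SD, and it is only a reading that 122 was calculated for a change-score test. The documents do not support a claim of bias over randomisations. The loss is one of precision, with sensitivity to whatever baseline difference chance produces.

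**What to change.** In {20a}, replace the assignment of the paired-samples t-test with a between-arm analysis: ANCOVA of week-24 LDL-C (or, equivalently for the treatment effect, of change in LDL-C) on treatment arm, with baseline LDL-C as a continuous covariate. Report the adjusted CBT-minus-control difference with its confidence interval. Use the same model, each with its own baseline value, for BMI, GSEs and QL-index. The unadjusted between-arm comparison can stay as supportive.

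The same sentence would cure the lack of a between-arm test, so both can be settled in one edit. The cost is that sentence and one degree of freedom. No new data or visits are needed, and the model is available in SPSS, the software that the article names. It should be fixed before the data are analysed by arm, so that the adjustment is not a choice made after seeing the results.

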### Trial design {8}

This study is a multicenter, prospective, randomized, controlled, open-label parallel-group superiority trial. Patients will be randomly allocated at a 1:1 ratio to evaluate the efficacy of CBT to lower blood lipids in ASCVD patients. The study protocol follows the Standard Protocol Items: Recommendations for Interventional Trials (SPIRIT) [18].

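### The test assigned to the endpoints neither compares the arms nor uses hospital; a between-arm model with a hospital term would supply the comparison and a modest gain in precision

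*Protocol article*

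**What the plan says.** Trial design {8}: "This study is a multicenter, prospective, randomized, controlled, open-label parallel-group superiority trial". Sequence generation {16a} and Concealment mechanism {16b} describe central allocation: "The EDC Trial Data system will randomly assign participants to either group in a 1:1 ratio". Neither section mentions balancing by hospital.

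Primary outcome measure: "The primary endpoint will be the mean change in LDL-C level", from randomisation to week 24.

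Statistical methods {20a} has two relevant sentences. The general one reads "Continuous variables will be expressed as mean ± SD and compared using the" t-test; it follows a sentence on categorical variables that refers to baseline. The specific one reads "The significance of primary and secondary endpoints will be evaluated with the paired-samples" t-test. No test in the section carries a hospital term, and section {20b} says that no additional analysis is planned.

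Recruitment {15}: "We will recruit participants in 6 hospitals". The list that follows has five names, and Study setting {9} names the same five.

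**The concern.** The primary hypothesis is about one arm relative to the other. A paired-samples t-test asks whether patients changed from baseline, and patients in a parallel-group trial are not paired across arms. As written, the assigned test cannot answer the primary question.

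Once a between-arm comparison is put in its place, the next question is what it should adjust for. Patients come from several hospitals, and hospital is recorded before randomisation at no cost. If hospitals differ in how much LDL-C changes over the 24 weeks, a plain two-sample t-test leaves that variation in the error term. The sample size has little slack: 150 per arm with 20% loss leaves 150 × 0.8 = 120 completers, against the 122 required.

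**Working it through.** **Inputs from the document.** 122 per arm, 80% power, one-sided 0.05, 150 per arm after allowing for 20% loss (Sample size {14}); a 20% reduction in LDL-C; no SD, no intraclass correlation and no between-hospital variance.

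**The plan's own figure.** The 122 cannot be reproduced, because no SD is given. Solving backwards for the standardised difference:

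d = (z₀.₉₅ + z₀.₈₀) / √(n/2) = (1.645 + 0.842) / √(122/2) = 2.487 / 7.810 = 0.318

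If the difference is read as 20 percentage points, the implied SD is about 62.8 points. With 120 completers per arm, power is Φ(0.318 × √60 − 1.645) = 79.4%.

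**Effect of a hospital term.** Let s be the share of the variance of LDL-C *change* that lies between hospitals. The document does not give s; 2% to 15% is assumed. Adjustment reduces the residual variance by the factor (1 − s), so

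power = Φ( d/√(1 − s) × √(n/2) − 1.645 ), with n = 122

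| Share s | Unadjusted SE relative to adjusted, 1/√(1 − s) | Power with hospital term | Unadjusted n per arm with the same information, 122/(1 − s) |
|---|---|---|---|
| 0 | 1.000 | 80.0% | 122 |
| 2% | 1.010 | 80.7% | 124 |
| 5% | 1.026 | 81.8% | 128 |
| 10% | 1.054 | 83.6% | 136 |
| 15% | 1.085 | 85.4% | 144 |

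These figures are for a two-sample comparison of change. They do not describe the paired test that the plan assigns.

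**Simulation check.** Six equal hospitals, 120 per arm, 4,000 runs per setting, two-sample t-test against a linear model with hospital as a fixed effect. The Monte Carlo standard error of each power figure is √(0.8 × 0.2/4000) = 0.6 points.

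- No hospital effect, allocation not balanced by hospital: 78.4% without the term, 77.7% with it. Nothing is gained.
- s = 5%: 80.1% to 80.9% without balancing by hospital, 79.4% to 80.5% with it. About 1 point.
- s = 10%: 80.1% to 82.2% without balancing, 80.4% to 82.7% with it. About 2 points, so the formula is somewhat optimistic here.
- One-sided type I error of the two-sample t-test: 0.046 to 0.054 without balancing by hospital, close to the nominal 0.05. If allocation were balanced by hospital, it would be 0.037 to 0.049, somewhat conservative.

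**Cost in degrees of freedom.** Five hospitals use 4 and six use 5, out of about 240.

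**Site count.** Recruitment {15} states six and lists five; Study setting {9} lists five.

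**The case against.** The strongest objection is that this is a condensed article with no analysis plan at hand, and that adjustment for centre is commonly settled in such a plan. Silence about a hospital term would therefore be no finding. That would be decisive if section {20a} had left the endpoint test open. It does not: it names the test, and the named test does not compare the arms. Since that sentence has to be rewritten anyway, the hospital term belongs in the rewrite. The objection does stand to this extent: leaving the term out is not an error in itself, and no stated stratification makes it obligatory.

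One could also say that the general sentence on continuous variables already provides a between-arm t-test for the endpoints. The sentence after it deals with the endpoints by name and assigns the paired test, so that reading is not secure. Even if it were right, the comparison would still make no use of hospital.

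Three stronger readings are tempting, and the document does not support them.

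- *All between-hospital variation in LDL-C stays in the error term.* The primary endpoint is a change from randomisation, so stable differences in level largely cancel. Only differences in the change itself remain.
- *Chance imbalance between hospitals distorts the result.* A hospital with 50 patients could split 18:32 (binomial 95% range), but this is random error that the standard error already covers. It is not bias.
- *Each hospital uses its own staff and its own drug treatment, so the effect must be large.* The text says only that healthcare providers give the control education and that both arms receive standard pharmacological treatment. Variation in the control education would act in one arm only, and an additive hospital term would not fully remove it.

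**Conclusion.** The point holds in a limited form. The more serious part is that the test assigned to the primary and secondary endpoints does not compare the arms. The hospital term is a secondary improvement in efficiency: power goes from 80% to about 81% to 85% if hospitals explain 2% to 15% of the variance of LDL-C change, with 2 points or less up to a 5% share and nothing if they do not differ. This rests on an assumed share and on an effect of 0.318 SD solved back from the sample size; the document supplies neither. A reader might infer that leaving hospital out invalidates or biases the trial. It does not: with no stratification stated, an unadjusted two-sample comparison keeps its type I error. The mismatch between six hospitals stated and five named is certain, whatever model is used, but it is an editorial matter and shows no loss of precision.

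**What to change.** Replace the paired-samples t-test in section {20a} with a linear model that compares the arms on LDL-C change from randomisation to week 24 and includes hospital as a fixed effect. Set a size rule for pooling hospitals with very few patients before the statistician is unblinded. Use the same form of model for the other continuous endpoints. State the true number of hospitals and name each one, so that the Study setting and Recruitment sections agree and the hospital term is well defined.

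The cost is analysis wording plus the 4 to 5 degrees of freedom. No new data are needed.

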### Objectives {7}

Aim 1: To determine the efficacy of mobile-based CBT interventions, compared with conventional interventions, in ASCVD patients receiving standard treatments;Hypothesis 1a (primary study hypothesis): a significant reduction in objective parameters, including LDL-C level, will be demonstrated in participants randomly assigned to the CBT group relative to participants in the conventional interventions group.

Aim 2: To improve our capacity to match patients to treatments more efficiently by identifying self-efficacy, and quality of life.Hypothesis 2a: a significant improvement in self-efficacy, and quality of life, measured by scales and questionnaires, will be demonstrated in participants randomly assigned to the CBT group relative to participants in the conventional interventions group.

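### One unadjusted p < 0.05 rule covers all eight secondary endpoints, with no decision visit, and leaves unclear what would establish Hypothesis 2a

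*Protocol article*

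**What the plan says.** All places are in the protocol article.

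- **Statistical methods {20a}.** One sentence treats all endpoints alike: "The significance of primary and secondary endpoints will be evaluated with the paired-samples" t-test. The next gives the threshold: a p-"value < 0.05 indicates statistical significance". Sidedness is not stated, and neither is any order, alpha split or exploratory label.
- **Secondary outcome measures.** Eight are listed: LDL below 70 mg/dL; that target combined with an HDL threshold; ratio of LDL to baseline; coefficient of variation of LDL; C-reactive protein; BMI change; GSEs score; QL-index score. None names a visit.
- **Outcomes {12}.** "Outcomes will be collected at baseline and again at 1, 3, and 6 months during the intervention period".
- **Primary outcome measure.** Here the time frame is fixed: "from randomization (day 0) to V5 (week 24) for a total of 6 months of treatment".
- **Objectives {7}.** LDL-C belongs to "Hypothesis 1a (primary study hypothesis"). Hypothesis 2a then states that "a significant improvement in self-efficacy, and quality of life, measured by scales and questionnaires, will be demonstrated" in the CBT group relative to the conventional group.
- **Section {20c}.** Analyses are run in both the full analysis set (FAS) and the per-protocol (PP) set unless otherwise noted. The FAS is the basis of the primary analysis.

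**The concern.** A 5% threshold carries a 5% error rate for one test. Applied separately to eight endpoints, the chance that at least one crosses it by luck is several times larger. Read literally, {20a} lets any such crossing be reported as a significant effect of CBT, whatever happens to LDL-C.

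Hypothesis 2a sharpens this. It is worded as something to be demonstrated, so it goes beyond description. Yet the plan does not say at which of three visits it is judged, or whether one favourable scale is enough. Both scales are scored by patients who know their allocation, and the Discussion accepts that expectancy effects may bias results. An open rule is least comfortable for endpoints of this kind. The LDL-C primary itself is unaffected: its endpoint and week are fixed.

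**Working it through.** **Plan's own figure.** The document gives no error rate for the secondary family, so there is none to reproduce. The only stated quantity is the 0.05 threshold.

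**Inputs from the document.** Eight secondaries; two scales under Hypothesis 2a; three post-baseline visits; threshold 0.05.

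**Assumptions.** No CBT effect on any endpoint. Each test is a valid two-sided 0.05 comparison between arms. Test statistics are jointly normal, with a common correlation between endpoints of 0, 0.5 or 0.8 and a correlation between visits of 0.5. The document gives no correlations, so the range is shown.

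**Step 1: independent endpoints, one visit.**

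- Either direction, eight tests: 1 − 0.95^8 = 33.7%.
- Favouring CBT, eight tests: 1 − 0.975^8 = 18.3%.
- Hypothesis 2a, either scale sufficient, either direction: 1 − 0.95^2 = 9.75%.

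**Step 2: correlated endpoints.** Simulated normal statistics (at least 200,000 draws per scenario). A result in either direction is any |z| > 1.96; one favouring CBT is any z > 1.96.

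| Scenario | Correlation 0 | 0.5 | 0.8 |
|---|---|---|---|
| 8 endpoints, 1 visit, either direction | 34% | 25% | 16% |
| 8 endpoints, 1 visit, favouring CBT | 18% | 13% | 8% |
| 8 endpoints, 3 visits, either direction | 66% | 53% | 36% |
| 8 endpoints, 3 visits, favouring CBT | 40% | 27% | 18% |
| 2 scales, 1 visit, either scale, either direction | 10% | 9% | 8% |
| 2 scales, 3 visits, either scale, either direction | 24% | 22% | 19% |

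For one two-sided 0.05 test the benchmarks are 5% in either direction and 2.5% favouring CBT.

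**Step 3: sensitivity.**

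- *Fewer effective endpoints.* If no patient meets the combined LDL and HDL target, seven endpoints remain. At correlation 0.5 the either-direction figures become 23% (one visit) and 49% (three visits).
- *Sidedness.* Sample size {14} uses one-sided 0.05. If {20a} meant the same, the chance of a false result favouring CBT at correlation 0.5 would be about 22% at one visit and 43% at three, against 5% for a single test.
- *Both scales required.* If GSEs and QL-index must both be significant at one named visit, the chance of a false claim cannot exceed that of a single test. There is no inflation.

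**The case against.** The strongest reply is that this is mostly silence. Only a condensed article is shown, and multiplicity rules, secondary time points and exploratory labels often sit in an analysis plan. That would be decisive if the article said nothing. It does speak: it sets one significance rule for primary and secondary endpoints together and attaches a formal hypothesis to two secondaries. What is criticised is that stated rule.

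Four further objections limit the point, and they stand:

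- **A false CBT benefit is not likely.** A reader might infer that it is. Under two-sided testing no scenario above reaches 50% in favour of CBT. The larger percentages count results in either direction, including those against CBT.
- **Testing at every visit is not planned.** {12} says when outcomes are collected, not that each visit gets its own test. The coefficient of variation of LDL is probably one value per patient. The three-visit rows are an upper scenario.
- **Hypothesis 2a may already require both scales.** It joins self-efficacy and quality of life with *and*. A reader might infer that either scale at any visit would do, but the text does not say so. It leaves the matter open.
- **Some ranking exists.** Hypothesis 1a is named primary, the conclusions are framed around LDL-C, and {20c} describes the PP set as a sensitivity analysis. Nothing says that a secondary can rescue a failed primary, but nothing prevents a secondary from being declared significant on its own.

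Finally, a paired-samples t-test compares visits within patients, not arms. The error rates above are therefore not those of the test as written. They describe what remains once that separate fault is corrected.

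**Conclusion.** The point holds at moderate weight. The stated rule gives the eight-endpoint secondary family a false-positive chance of about 25% at a single visit (16% to 34%), five times the nominal 5%. In favour of CBT it is about 13% (8% to 18%), also about five times the 2.5% of one test. Hypothesis 2a carries about 9% if either scale suffices at one visit, and no inflation if both are needed.

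These figures rest on no true effect, valid two-sided between-arm tests and assumed correlations. They do not show that a spurious CBT benefit is probable, and they do not touch the primary endpoint. The defect is that the plan calls every secondary crossing significant while leaving the visit, and the condition for Hypothesis 2a, to be settled later.

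**What to change.** In {20a}:

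1. Make week 24 the decision visit for every secondary endpoint, with months 1 and 3 descriptive.
2. State that Hypothesis 2a is claimed only if both GSEs and QL-index are significant at week 24 in the FAS. Fixing the order of the scales, or testing each at 0.025, would also work.
3. Preferably test Hypothesis 2a only after a significant LDL-C primary. This is one acceptable option. Without it, error is controlled within each hypothesis but not across the two.
4. Label the other six secondaries and all PP results exploratory, reported as estimates with 95% confidence intervals.
5. Limit the p < 0.05 statement to the primary and Hypothesis 2a, and reconcile its sidedness with {14}.
6. Replace the paired test with a between-arm analysis. This is a separate correction, but the error rates here depend on it.

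Items 1 to 5 cost wording only: no patients, visits or data. The downside is that fewer results can be called significant. If the LDL-C gate is used, no confirmatory claim on the scales is possible when LDL-C fails.
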